## 1. Introduction

Crohn's disease is an incurable recurrent inflammatory bowel disease (IBD). Treatment is focused on managing the underlying inflammation or disease activity in the gastro intestinal tract, and thereby improving health related quality of life (HRQoL). However, disease activity is not the sole determinant of HRQoL, and multiple studies and reviews looking at interventions to improve all aspects of HRQoL, including dietary interventions, distance self-management and psychological therapy have all identified a need for interventions that are simple, safe, low cost and can improve several aspects of health and wellbeing. Exercise as an intervention is a candidate intervention.

Most research has focused on light to moderate aerobic exercise in IBD with a few studies investigating resistance type exercise. However, there appears to be no research study investigating whole body vibration (WBV) which has the potential to affect HRQoL by positively influencing inflammation, fatigue, bone mineral density, muscle strength, aerobic capacity, and pain. Being able to prescribe WBV exercise for IBD patients as an adjunct therapy could improve the patient's HRQoL at a lower economic cost.

In the last decade vibration stimulation or so-called vibration therapy/exercise has become increasingly popular as an exercise technique in healthy individuals as well as for health conditions such as fibromyalgia and has been proposed as a relevant management technique for COVID19. Whole body vibration involves standing statically on an oscillating (i.e. vibrating) platform. Because the structure of the human body is not rigid, muscles and tendons act as springlike elements that store and release mechanical energy. This can result in increased muscle activity which can also increase heat production as well as increase blood flow.

Investigations using novel devices developed by one of the Co-Investigators have shown that in the upper limb muscles, vibration exercise superimposed on isometric contractions is able to generate significantly higher level of neuromuscular load leading to muscle activity in healthy individuals. Further, in the lower limbs we have shown that vibration superimposed on isometric contraction is able to induce significantly higher levels of neuromuscular activity compared to isometric contraction alone and that this increased neuromuscular activity is dependent on the level of muscle stretch, vibration frequency as well as amplitude. This demonstrates that static WBV exercise produces a greater stimulus than static exercise alone.

There are however barriers to exercise interventions - with time constraints being one of them. Research by Tew et al. (2019), has demonstrated that adults with IBD did not meet the recommended physical activity guidelines and that abdominal and joint pain was the greatest reason for limiting their physical activity followed by fatigue/tiredness and increased toilet urgency.

Regarding time constraints: WBV is a strong potential candidate for an exercise intervention in this context as most research involving WBV have been of shorter durations 4-6 weeks compared to 10-12 weeks with aerobic exercise interventions. In addition, each individual training session tends to be of a much shorter duration; 10-15 minutes compared to 30 minutes of aerobic exercise.

In terms of pain management and treatment: it is hypothesised that WBV exercise could be utilised in a fashion similar to transcutaneous electrical nerve stimulation (TENS) in order to reduce the perception of pain. A systematic review and meta-analysis on the effects of WBV exercise on chronic musculoskeletal pain concluded that “positive effects of vibration exercise on chronic musculoskeletal pain are evident, and long durations of WBV exercise(s) could be especially beneficial”. In addition, research in fibromyalgia patients also found a reduction in pain after 6-weeks of WBV intervention.

Vibration exercise has been shown to improve heart rate variability (HRV) in a range of population, including the elderly. An increase in HRV has been shown to be linked to a reduction in pain, which could benefit patients with IBD.

Limitations to physical activity and pain in IBD cohorts is in part driven by active inflammatory processes, several studies using WBV have demonstrated an increase in anti-inflammatory cytokines in particular IL-10 in various health conditions including fibromyalgia and osteoarthritis. We propose to assess whether this is upheld in Crohn's disease.

Fatigue is a large determinant of HRQoL, as well as a barrier to physical activity as described above. 6 weeks of WBV exercise has been shown to improve fatiguability in different conditions including fibromyalgia and older adults. We know fatigue is multifactorial and includes an aspect of the mental health of the patient, therefore during the study we will ask our patients to undergo a Hospital Anxiety and Depression Scale Questionnaire which is validated in the Inflammatory Bowel Disease Population.

In conclusion: there are several potential mechanisms of action for WBV exercise to improve symptoms and HRQoL of inflammatory bowel disease sufferers. The proposed study would be the first study to explore the concept of using WBV exercise as a potential adjunct therapy in Crohn's disease to improve HRQoL.

## 2. Aims and Objectives

### 2.1. Trial/Study objectives

- The primary objective, or principal research question is does WBV exercise improve health related quality of life (HRQoL) for patients with Crohn's disease.
- Secondary Objective: The secondary research questions are:
  - ! Does WBV improve general cardiovascular health from baseline in Crohn's patients?
  - ! Is Crohn's disease activity impacted by WBV?
  - ! Does WBV in Crohn's patients significantly alter their blood markers of inflammation?
  - ! Does WBV alter bone health markers in CD patients?
  - ! Does WBV impact on subjective perception of fatigue, or objective measurement of neuromuscular fatigue?
  - ! Does WBV impact on perception of pain in CD patients?
  - ! Does WBV impact on markers of anxiety or depression in this population?

- 
- Primary End Point: the primary end point is an improvement in the IBD-Q - with an objective improvement of 16 points.
- Secondary End point: The secondary end points are:
  - ! Improvement in heart rate variability, resting blood pressure or sub maximal Chester step test
  - ! A static or improved partial Harvey Bradshaw index and faecal calprotectin
  - ! A significant delta in blood TNF- $\alpha$ , IL-6, IL-17A, IL12/IL-23, IL-10, TGF- $\beta$ , C-Reactive protein between the beginning and end of the study
  - ! An improvement in serum P1NP
  - ! The difference between subjective fatigue at the start and end of study, as well as a difference in objective neuromuscular fatigue between the start and end of the study
  - ! Obtaining granularity of patients thoughts, experience and feelings towards WBV as an intervention for the adjunct management of Crohn's disease

### 3. Methods

#### 3.1. Study Design

VECTOR is a randomised controlled trial.

#### 3.2. Trial/Study Setting

VECTOR recruitment will take place at selected NHS gastroenterology clinics within travelling distance from the University of Hertfordshire Institute of Sport. The baseline, WBV exercise and exit visits will take place in the Institute of Sport, De Havilland Campus, University of Hertfordshire. The lifestyle education for the control arm will take place remotely (on zoom).

#### 3.3. Trial/Study Participants

Adults aged  $\geq 18$  years with mild to moderate active CD (Partial Harvey Bradshaw Index of 5-16) will be identified from IBD/Gastro clinics and approached by the clinical team or designated research nurse from 3 NHS sites during the participant gastroenterology outpatient appointment. They will be given the PIS and consent form if interested and asked for contact details so the UH research team can contact them to arrange the initial screening, and subsequent baseline assessment and randomisation visit at the University of Hertfordshire. This information will be emailed from one of the clinical team on their [nhs.net](https://nhs.uk) account to [name] on [[contact]](mailto:[contact]). [name] will then liaise with the Senior Research Assistant for an appropriate visit time and slot for the participant screening and baseline visit.

Inclusion criteria:

Is the patient aged between 18 and 65 years old (inclusive)?

Has the patient had a clinical diagnosis of Crohn's disease for at least 4 weeks before the screening visit?

Does the patient have either mild or moderate Crohn's disease based on a partial Harvey Bradshaw Index (5-16)?

Does the patient have a faecal calprotectin  $< 250$  mcg/g recorded no greater than 4 weeks before the screening visit?

Have the patient's medications been stable (i.e., unchanged) for at least 4 weeks before the screening visit?

Is the patient capable of giving written informed consent?

Is the patient capable of completing the study questionnaires?

Is the patient able to travel to the research sites for all assessment visits and exercise sessions?

Exclusion criteria:

Does the patient have any absolute contraindications to exercise testing and training?

Does the patient have any coexistent serious autoimmune disease?

Does the patient have major surgery planned in the first 3 months following the anticipated baseline visit date?

Is the patient pregnant?

Is the patient female and planning pregnancy within the first 3 months following the anticipated baseline visit date?

Does the patient think that they will be unable to tolerate the venepuncture requirements of the study?

Does the patient lack sufficient venous access to meet the blood sampling requirements of the study?

Is the patient participating in another clinical trial for which concurrent participation is deemed inappropriate?

Is the patient unable to consent?

#### 4. Trial/Study Procedures

##### 4.1. Trial/Study Setup

The trial setup will proceed as follows (further details in GANTT chart below):

1. Obtain ethical approval, set up trial steering group and begin recruiting (Months 1-3)
  - a. Sign contracts
  - b. Set up trial governance
  - c. Collate lifestyle education information from publicly available Crohn's and Colitis UK Patient information.
2. Recruit and enrol 55-60 participants (Months 4-12)
  - a. Undertake baseline assessments
  - b. Deliver exercise intervention and lifestyle education programme
  - c. Undertake post intervention assessments and participant interviews
3. Complete recruitment (12-27 months)
  - a. Finish recruiting at 27 months (168 participants in total)
  - b. Finish baseline assessments
4. Complete measurements of secondary outcome measures (28-31 months)
  - a. Complete interviews
5. Analysis of data, dissemination and report writing (32 – 36 months)
  - a. Bloods analysis
  - b. Interview analysis
  - c. Data analysis
  - d. Dissemination – organising workshops to disseminate results

[figure not shown]

Caption

## 4.2. Recruitment

### 4.2.1. Participant Identification

The primary mode of recruitment will be via the IBD clinics at recruiting NHS Hospital Trusts. A member of the clinical team will identify potentially eligible patients via review of medical notes ahead of gastroenterology clinics. Potentially eligible, interested participants will be given the Participant Information Sheet (PIS) to take away and read. Potentially eligible, interested participants will then provide e-consent to share their contact details with the research team using Contact Details Consent Form on the REDCap database. They can then be contacted by a member of the research team within 28 days to organise the screening, trial consent and randomisation visit.

## 4.3. Screening

Potentially eligible patients will be initially screened for participation in the study by a research nurse with eligibility confirmed with a delegated clinical co-investigator. Once e-consent to share participant contact details has been gained, the baseline/screening visit must be performed with 28 days with the research team. During this screening ALL participants who are biologically able to become pregnant will be asked to complete a pregnancy test as part of the eligibility criteria, as pregnancy or planned pregnancy within 3 months of enrolling in the study is an exclusion criteria.

### 4.3.1. Informed Consent

There are two stages of informed consent. As stated above, participants are e-consented to share their contact details with the research team using Contact details consent form on the REDCap database. They are reminded of the attributes of the study at this stage.

Following screening, informed e-consent to take part in the study is gained via the VECTOR consent form on REDCap, with the research team. It is the responsibility of the Investigator, or appropriately trained person delegated by the Investigator as documented in the site delegation log, to obtain informed consent from each participant prior to any participation or trial/study specific procedures. This should follow adequate explanation of the aims, methods, anticipated benefits and potential hazards of the trial/study.

The Investigator (or other qualified person on the delegation log) will explain to the potential participant that they are free to refuse any involvement within the trial/study or alternatively withdraw their consent at any point during the trial/study and for any reason.

If there is any further safety information which may result in significant changes in the risk/benefit analysis, the PIS and Vector Consent Form will be reviewed and updated accordingly. All participants that are actively enrolled on the trial/study will be informed of the updated information and given a revised copy of the PIS in order to confirm their wish to continue on the trial/study.

Further guidance can be found at: <http://www.hra.nhs.uk/research-community/before-you-apply/participant-information-sheets-and-informed-consent/>

## 4.4. Allocation/Randomisation

### 4.4.1. Randomisation Procedures

Once screening procedures have confirmed the participant's eligibility to enter the trial/study and the participant has provided informed consent, the process of randomisation can commence.

The participants will be 1:1 randomised using REDCAP (an automated process) after screening confirmation and consent, this process is immediate and will be done whilst the participant is undergoing baseline measurements (as defined below). This is done by the member of the research team undertaking the screening and consent (e.g. the research assistant). As the trial cannot be blinded there is no code break. Once the participant has been successfully randomised in VECTOR, the enrolment of this participant must be documented within an enrolment log.

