| Intervention       | 
After initial assessments (bloods for inflammatory markers, Chester step test, blood pressure, heart rate, faecal calprotectin, electromyograph of the thighs), participants will be randomly allocated to either a 6 week whole body vibration course and lifestyle education programme or a control group with lifestyle education. The whole body vibration means the participant is supervised crouching (static squat) on a vibration plate for 60 seconds at a time, 6 times, with 60 second rests in between, three times per week.
 
Both groups will get the lifestyle education programme which will equate to 30 minutes per week with two sessions on healthy eating, 3 sessions on physical activity and 1 round up or smoking cessation education. Both groups will undertake an electromyograph of their lower limbs (thigh muscles) at the beginning and end of the study. Both groups will undertake health related quality of life questionnaire (IBD-Q), HADS and IBD-Fatigue questionnaires, at the beginning and end of the study, as well as scoring their pain and level of physical activity daily one week prior and 1 week after the 6 weeks intervention, via REDCAP. The first 15 participants will be invited to participate in semi-structured interviews designed to gain feedback about how they felt the intervention went. Both groups will be asked to wear a chest strap and watch between the hours of 7am – 7pm, for three consecutive days following their first and last visit to the University of Hertfordshire. This is to assess heart rate variability.
 |

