#### 4.5. Baseline

Baseline tests are:

1. Submaximal Chester Step Test
2. Anthropometry: Weight, Height, heart rate variability, blood pressure
3. \*Bloods for inflammatory markers as described above
4. Electromyography (EMG)
5. Health Related Quality of Life Questionnaire (IBD-Q)
6. HADS questionnaire
7. IBD-Fatigue Questionnaire
8. Faecal calprotectin (done as part of usual care at the NHS site, and only the result is used, no stool samples will be handled by the research team)
9. REDCAP participant 7 day input of pain perception and physical activity.

\*12ml of whole blood will be taken via venipuncture, by a team member training in phlebotomy who is on the delegation log. The blood will be centrifuged on site, the cellular component destroyed and discarded as per Health and Safety guidelines, the remaining acellular plasma will be stored in vials labelled with the participant pseudoanonymised number at -80 degrees centigrade, and then once all samples are collected from the study, they will be sent to [name] at The University of Central Lancashire by courier.

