## 11. Data Protection and Participant Confidentiality

### Confidentiality

The Investigator has a responsibility to ensure that participant anonymity is protected and maintained. They must also ensure that their identities are protected from any unauthorised parties. Information with regards to study participants will be kept confidential and managed in accordance with the Data Protection Act, NHS Caldicott Guardian, The Research Governance Framework for Health and Social Care and Research Ethics Committee Approval.

Patient identifiable information shared across the research team is limited to name, email address and phone number. Hospital number and date of birth is collected on CRFs at the NHS site - but pseudo-anonymised with a patient research number. Only members of the research team will have access to this information.

The CI is custodian of the data.

The participants can withdraw at any stage, but any data collected up until the point of the withdrawal will still be used within the study. The patients will be asked for a preference of contact details and can withdraw this at anytime by informing the research team.

All data will be anonymised within any publications or dissemination of findings. The CI is the data controller and the research teams both on NHS site and at the University of Hertfordshire are the data handlers. The responsibility for data quality is described above. DPIAs will be completed for each NHS site with the University of Hertfordshire.

**Case Report Form (CRF)** forms are visit specific and are completed by the research assistant or member of the research team undertaking that particular visit parameter.

The Baseline and exit CRFs will record the data as described above

The WBV CRFs will confirm the number of WBV 60 seconds undertaken and confirmation of the lifestyle education delivery.

It will also confirm any AEs during the WBV intervention.

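### Randomisation is run while baseline is still being measured in an unblinded trial, so the self-reported baselines, including the primary IBD-Q, can be completed with the allocation known

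*Protocol*

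**What the plan says.** Section 4.4.1 of the protocol starts randomisation once eligibility and consent are in place. It adds that "this process is immediate and will be done whilst the participant is undergoing baseline measurements", and points to the list in section 4.5 for what those measurements are. That list holds the step test, heart rate variability, blood pressure, bloods, EMG, IBD-Q, HADS, IBD-Fatigue and the 7-day pain and activity diary. Section 4.4.1 also states: "As the trial cannot be blinded there is no code break". The team member who screened and took consent runs the randomisation, with the research assistant given as an example.

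The Intervention row of the Trial/Study Summary gives another order. It lists initial assessments ending in "electromyograph of the thighs), participants will be randomly allocated". The questionnaires, diary and wearable recording are not in that list. The same row has participants "scoring their pain and level of physical activity daily one week prior and 1 week after the 6 weeks intervention", and has them wear a chest strap and watch "for three consecutive days following their first and last visit to the University of Hertfordshire" to assess heart rate variability.

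Section 4.3.1 requires consent before any trial-specific procedure. Section 6.3 estimates the effect on every outcome as the difference between groups in change from baseline.

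**The concern.** In an unblinded trial, the baseline is protected by completing it before anyone at the visit knows the arm. A participant who has just learned the allocation may, through disappointment or anticipation, answer a quality-of-life or fatigue questionnaire differently, or change activity during a diary week. The primary outcome is self-reported, and baseline is one half of every change score. A shift introduced this way is bias: a larger sample does not reduce it, and neither does an intention-to-treat analysis. If a model adjusts for baseline, it would be adjusting for a value measured after randomisation. A statistical analysis plan cannot repair this afterwards, because it cannot change when the baseline was taken.

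**Working it through.** **Order of events.** There is no stated figure to reproduce, so the check compares the protocol's own timings.

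| Measure | Summary, Intervention row | Sections 4.4.1 and 4.5 | Position relative to randomisation |
|---|---|---|---|
| Step test, bloods, blood pressure, EMG | Before allocation | Among the measurements during which randomisation is run | Contradictory |
| IBD-Q, HADS, IBD-Fatigue | At the start of the study; not tied to allocation | Same | Not placed before it anywhere |
| 7-day diary | The week before the intervention | Listed as a baseline test | After it, on the stated timings |
| Wearable heart rate variability | Three days after the first visit | Heart rate variability listed among visit measures | Wearable recording after it; in-visit value undetermined |

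**Diary.** It is a trial procedure, so under section 4.3.1 it cannot start before trial consent. The earlier e-consent covers only the sharing of contact details. Section 4.2.1 describes one visit for screening, trial consent and randomisation. Section 4.6 gives the vibration arm 20 visits, 18 of them for the intervention; 20 − 18 = 2, which leaves one baseline and one closing visit. A seven-day diary that starts at or after consent at that first visit therefore runs after randomisation.

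**Wearable recording.** It follows the first visit, which is the randomisation visit by the same count.

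**Effect on the estimate.** Let d be an allocation-related shift in one arm's mean baseline that is absent at follow-up.
- Difference in change: bias = d in absolute value.
- Baseline-adjusted analysis, with equal baseline and follow-up standard deviations and correlation r: bias is about r × d. Section 6.3 does not specify such a model.

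**Illustration of scale.** From the protocol: 168 participants at 1:1, so 84 per arm; a 16-point IBD-Q target; significance at 0.05. Assumed: a two-sided test, a standard deviation of change of 30 to 40, no dropout, and the values of d.

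SE = SD × √(2/84), which is 4.63 at SD 30 and 6.17 at SD 40.

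False-positive rate = 1 − Φ(1.96 − d/SE) + Φ(−1.96 − d/SE).

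| Assumed d | d/16 | False-positive rate, SD 40 to SD 30 |
|---|---|---|
| 2 | 12.5% | 6.2% to 7.2% |
| 4 | 25% | 9.9% to 13.9% |
| 8 | 50% | 25% to 41% |

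If the shift runs against the intervention, d = 4 turns a true 16 into 16 − 4 = 12 points, and power falls from 74%–93% to 49%–74%. With baseline adjustment at an assumed r of 0.5, the 4-point bias becomes 0.5 × 4 = 2 points.

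**The case against.** Several stronger readings are tempting, and the documents do not support them.

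- **That the IBD-Q comes late in the visit.** It is fifth in section 4.5, but that list is an inventory. It includes faecal calprotectin, which is measured at the NHS site as usual care. Only the absence of any rule placing the IBD-Q before allocation stands.
- **That the step test is compromised.** The Summary puts it before allocation. For this and the other physical measures the finding is a contradiction to resolve.
- **That participants know their arm when they answer.** Section 4.4.1 says when REDCap is run, not when the result is disclosed. Influence is possible, not shown.
- **That one person randomises and measures.** The research assistant is only an example in section 4.4.1. Section 11 has case report forms "completed by the research assistant or member of the research team undertaking that particular visit parameter", so two people could work in parallel. No blinded or separate baseline assessor is named, however.
- **That baseline heart rate variability is necessarily post-randomisation.** Section 4.5 also lists it among visit measures, and the protocol does not say which recording is analysed.

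On the diary, section 3.3 separates an initial screening from the baseline and randomisation visit. Consent a week or more ahead could let the diary come first, but no section describes that sequence.

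On size, the shifts are assumptions. If altered reporting persists to the closing visit, it cancels partly or wholly in the change score. None of this removes the central point: section 4.4.1 as written permits the primary baseline to be completed after allocation.

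**Conclusion.** The point holds as a sequencing fault with possible bias. Following section 4.4.1 leaves the IBD-Q, HADS and IBD-Fatigue baselines open to knowledge of the allocation, and the Summary contradicts that section without protecting the questionnaires. The diary falls after randomisation on the stated timings. So does the wearable recording, unless the in-visit heart rate variability is the analysed baseline. The resulting bias equals the differential baseline shift, provided that the shift is absent at follow-up. Its size and direction cannot be derived from the protocol, and the error rates above only show that a few points would matter. A reader might infer that the primary result is already biased; the documents show only that the plan does not prevent it.

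**What to change.** 1. Reconcile the Summary and section 4.4.1 to one order: consent, all in-visit baseline measures (IBD-Q, HADS, IBD-Fatigue, step test, blood pressure, EMG, bloods and any in-visit heart rate variability), then randomisation.
2. Enable the REDCap randomise step only when those forms are complete and saved.
3. State whether the in-visit or the three-day wearable recording is the analysed heart rate variability baseline.
4. For the diary, and for the wearable recording if it is analysed, choose one of two courses. Either randomise remotely in REDCap after those days are recorded and then notify the participant, or label the measures as post-randomisation and compare follow-up values only.

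Items 1 to 3 cost a wording change and a form-order lock. Under item 4, waiting delays arm-specific bookings by about a week and may lose some consented participants before randomisation. Labelling avoids both costs but gives up the change-from-baseline analysis for those secondary measures.

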## 8. Quality Assurance and Control

### 8.2. Risk Assessment

This study is determined as low risk; the rights and safety of participants will be upheld throughout. All participants will perform a warm up and cool down for every WBV session, however muscle soreness has been identified as a risk factor. WBV is low intensity and undertaken with 1:1 supervision, which with the warm/cool down reduces this risk. The research assistant will be first aid trained, and there is a defibrillator on site. All risks associated with the study have been assessed using the University of Hertfordshire's Life and Medical Sciences (LMS) risk assessment form.

The project concept is being supported by an established and experienced Trial Management Group and the Lead PI is being supported and mentored to run the trial via the CI who has extensive experience in this style of research.

The Trial is supported by the UH CTSN in terms of QC and QA to ensure the study is performed and data generated/documented and reported in compliance with the principles of GCP, they are also reportable to regarding study recruitment rates.

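### Section 4.4.1 calls the whole trial unblindable, though this is true only of participants and session staff; EMG and HRV processing and the exit visit lack cheap masking

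*Protocol*

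**What the plan says.** On blinding, the protocol has one sentence, in section 4.4.1: "As the trial cannot be blinded there is no code break". It does not distinguish participants, session staff, exit assessors, signal processing and the laboratory. The same section has randomisation done by whoever carries out screening and consent, with the research assistant as the example, while baseline measurements are under way.

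On who records the data, the Case Report Form paragraph in section 11 says that visit-specific forms "are completed by the research assistant or member of the research team undertaking that particular visit parameter". It then describes baseline and exit forms, and separately the WBV session forms. Section 8.2 says that "WBV is low intensity and undertaken with 1:1 supervision" but does not name the supervisor.

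On the questionnaires, section 4.7 lists the IBD-Q, HADS and IBD-Fatigue among the items of the closing visit at the University. The Trial/Study Summary has both groups undertake these questionnaires at the start and end, as well as "scoring their pain and level of physical activity daily one week prior and 1 week after the 6 weeks intervention, via REDCAP". In section 4.7 only the seven-day pain and activity record is labelled as participant input to REDCap.

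**The concern.** Whether a trial can be blinded is a separate question for each role. Here participants and session supervisors cannot be masked. Someone turning an EMG trace or a three-day heart rate recording into a summary value can be, because the recording can be handled under a participant number. A blanket statement closes off masking where it is feasible.

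Two things are at stake. First, the primary endpoint is subjective. If the IBD-Q is answered with staff present who delivered the treatment, social pressure or prompting may differ between arms. Second, HRV and objective neuromuscular fatigue are named secondary endpoints, and in an open-label trial they are part of what could corroborate a self-reported benefit. They do that better if whoever derives them does not know the arm.

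**Working it through.** The plan gives no figure on this point, so the check sets the sections side by side.

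**1. Who must know the allocation.** The intervention is static squatting on a vibrating platform (section 4.6). The comparator is the same programme without WBV (Summary, Comparison), with education by video call (sections 3.2 and 4.6). There is no sham. Participants and session staff therefore necessarily know the arm. Nothing in the design forces the same on anyone processing signals or assaying samples.

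**2. What protects each exit item in section 4.7.**

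| Item | Source of the value | Protection stated |
|---|---|---|
| 1. Chester step test | On-site visit, tester not named | None |
| 2. Weight, height, HRV, blood pressure | On-site visit; HRV also by chest strap and watch over three days (Summary) | HRV capture is by device; processing not addressed |
| 3. Bloods | Vials under a pseudonymised number, sent to another university | Coded; not stated whether the laboratory receives allocation |
| 4. EMG | On-site visit | None; processing not addressed |
| 5. IBD-Q (primary) | Participant questionnaire | Mode and setting of entry not fixed |
| 6. HADS | Participant questionnaire | As item 5 |
| 7. IBD-Fatigue | Participant questionnaire | As item 5 |
| 8. Faecal calprotectin | Result from the NHS site | Samples not handled by the research team |
| 9. Pain and activity diary | Participant in REDCap | Participant entry |

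Items 3, 8 and 9 have some separation from research staff, which leaves 9 − 3 = 6 without any that is stated. (Within item 2, height and weight leave little room for influence.) The partial Harvey Bradshaw Index is marked as collected before and after in section 6.1, is not in the section 4.7 list, and has no named assessor.

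**3. Who may run the exit visit.** Section 4.4.1 gives the research assistant as an example of the person who randomises and so knows the allocation. Section 11 allows the research assistant, or whichever team member does that measurement, to complete the form. Section 8.2 mentions the research assistant's first-aid training in the paragraph on WBV session risk. Together these permit overlap between session staff and exit assessors. No section states the overlap, and none rules it out.

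**4. Contact before the exit visit.**
- WBV arm: 3 sessions per week × 6 weeks = 18 on-site sessions, matching section 4.6. Education is 18 × 10 = 180 minutes.
- Control arm: 6 individual video sessions. Education is 6 × 30 = 180 minutes.

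Education time is equal. The contrast is 18 in-person supervised sessions against 6 one-to-one remote ones, so controls are not without staff contact.

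**5. Size.** The documents contain no estimate of bias from staff presence or unmasked processing, so none is calculated.

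**The case against.** The strongest reply is that the sentence in section 4.4.1 only explains why there is no emergency unblinding, and does not forbid masked processing. Masking of signal processing might also be set out in a statistical analysis plan, which was not available. Both points are fair. But the sentence is the protocol's only position on blinding, it is worded for the whole trial, and it is inaccurate as worded.

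Several stronger readings are tempting and are not supported:

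- A reader might infer that the protocol assigns the exit forms to the session team. It does not. Section 11 permits this without saying it, and section 8.2 does not name the supervisor.
- A reader might call the exposure of the primary outcome avoidable assessor bias. For a self-reported questionnaire the unblinded participant is the assessor. Private entry limits staff presence and prompting; it does not remove participants' expectations.
- A reader might assume that staff elicit the IBD-Q answers. Eligibility requires patients to be able to complete the questionnaires, and the mention of REDCap in the Summary ends a sentence that also lists them. Participant entry may already be intended, but it is not stated clearly.
- A reader might take all the objective endpoints to be unprotected. Bloods are coded and sent elsewhere, and calprotectin is an NHS-site result.
- A reader might express the bias as a share of the 16-point IBD-Q target. Any such figure would rest entirely on an invented number of points.

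What stands of the objection is that the point is smaller than it first looks. It does not remove the case for correcting the statement and fixing the procedures.

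**Conclusion.** The point holds in a limited form. The blanket statement is right for participants and session staff and wrong for EMG and HRV processing, which the protocol leaves unmasked. The protocol also leaves open that staff who know the arm, or who supervised the sessions, handle the exit visit at which the primary IBD-Q is completed.

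The gain from a change is real but cannot be quantified from the documents. It covers processing of EMG and HRV, staff presence and prompting for three questionnaires, and conduct of the step test, blood pressure and partial Harvey Bradshaw Index. Expectation bias in the IBD-Q remains afterwards and should be acknowledged.

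The conclusion assumes that EMG and HRV recordings need some processing after capture, which the protocol does not describe, and that no other trial document already masks it. It is a cheap improvement, not a flaw that invalidates the primary comparison.

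**What to change.** **Section 4.4.1.** Limit the statement to participants and session staff. Add that EMG and HRV signals are processed under participant number, with no access to allocation until those data are locked. Confirm that the laboratory receiving the coded bloods is not sent the allocation.

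**Sections 4.5 and 4.7.** State that participants enter the IBD-Q, HADS and IBD-Fatigue themselves in REDCap before meeting staff, and that staff neither enter nor discuss the answers. At baseline, section 4.3.1 requires consent before any study procedure, so entry there should come directly after e-consent and before randomisation and the other measurements.

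**Exit assessments.** Name who does them. Where existing staffing allows, have the step test, blood pressure and partial Harvey Bradshaw Index done by a team member who did not supervise that participant.

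**Limitation.** Acknowledge that the self-reported primary outcome stays open to participant expectation.

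**Cost.** Protocol wording, three questionnaires added to a REDCap system already in use for the diary, and restricted access to the allocation field for whoever processes the signals. Some participants will need help with online entry. No additional assessor is required.
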